**Figure 2 Fig2:**
[figure not shown]
**Schematic representation of trials in General inhibition training.**

*Alcohol No*-*Go training* (*based on* 29; *see Figure*3): Participants in this group will respond to a letter that will be presented in the corner of an alcohol-related or neutral picture. The letter P is the ‘Go’ cue which signals that participants should respond, whereas the letter R is the ‘No-Go’ cue which signals that they should not respond on that trial. The Go cue will always appear in the corner of neutral pictures and the No-Go cue will always appear in the corner of alcohol pictures. Each block contains 200 trials: 100 Go and 100 No-Go.

**Figure 3 Fig3:**
[figure not shown]
**Schematic representation of trials in Alcohol No-Go training.**

*No training* (*control*) *group*: Participants will perform 200 trials of a forced choice reaction time task in which they rapidly categorise alcohol-related and neutral pictures by pressing the keys ‘X’ and ‘M’. They will never be required to inhibit their responses.

### Procedure

Figure 4 shows a flow chart of the flow procedure.

**Figure 4 Fig4:**
[figure not shown]
**Flow chart of trial procedure.**

#### Assessment phase

Participants who register interest in the study will complete a brief email screen to assess eligibility before attending an initial appointment. They will provide informed consent, before completing a questionnaire battery consisting of the TLFB, AUDIT, BIS and TRI. Participants will then be asked to set up their own account on the DYD website. DYD is an interactive web-based intervention for people who want to cut down on drinking [51]. Participants will complete the ‘quick visit’ option on the site. This involves participants making a decision about whether they need to cut back on their drinking and if so, they make a goal to cut back on drinking for the next week. They will also be asked to use an online drinking diary on the site to keep a record of their alcohol consumption over the next week. Participants will then leave the laboratory and return one week later. Participants who do not wish to reduce their drinking will be able to withdraw at this point.

Upon their return participants will check their online drinking diary and use this to complete a paper-and-pencil TLFB for the previous week. Participants will then be asked to re-affirm consent that they wish to continue in the study; if they wish to withdraw they will receive compensation (£20) before release. Participants who choose to remain in the study will complete baseline measures of the general SST, cue-specific SST and the AV-IAT in the laboratory. Participants will be told that they should continue to use the DYD drinking diary for the remainder of the study, and they should complete training tasks by following Internet links that will be emailed to them.

#### Training phase

Participants will be randomised to one of four experimental groups: (1) Cue-Specific inhibition training, (2) General inhibition training, (3) Alcohol No-Go training or (4) Control (no training). Participants will complete up to 14 web-based training sessions during the four weeks of the training phase by following links that will be emailed to them every other day. In order to increase compliance, participants will be informed that if they miss a session on a particular day they can complete the session on the following day, but they must complete at least two sessions per week and there must not be a gap of more than three days between sessions. If they have not completed a session before the next one is due, a reminder email will be sent. They will be informed they can access the training at any point between midday to midnight.

Each time they log on to the site they will be asked how much alcohol they have consumed since their previous session (in UK units). A new email will be sent out containing the link for each assessment. Participants will also be provided with an email address and phone number in case they encounter any problems, and they will be contacted after two weeks by email to ensure that they are not experiencing problems. If participants have completed fewer than half of the required sessions at this stage (<4) they will be withdrawn from the study. These measures are in place to ensure high rates of compliance [69]. After the four weeks of training sessions, participants will return to the laboratory and complete follow up questionnaires including the AUDIT, TLFB and a measure of how motivated they were to reduce their alcohol consumption during the previous four weeks. They will also complete the SSTs (cue-specific and standard) and AVIAT in the laboratory once more. They will be reimbursed for their participation up until that point (£40-£130, depending on the number of training sessions completed) and partially debriefed. Participants are not told which group they were allocated to at this point.

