#### Primary analyses

Primary and secondary outcome measures will be analysed using mixed-design ANOVA with a between-subject factor of treatment condition (4: Cue-Specific inhibition training, General inhibition training, Alcohol No-Go training, Control) and a within-subject factor of time (3: baseline, two weeks into training, four weeks into training).

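### Withdrawing randomised participants with fewer than four sessions at week 2 restricts the primary comparison to those who meet a session threshold, and may bias it

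*Protocol article*

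**What the plan says.** All of this is in the protocol article.

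- **Order of events.** The Training phase section opens with allocation: "Participants will be randomised to one of four experimental groups". Sample size and randomisation confirms that this follows the one-week monitoring period.
- **Planned exposure.** "Participants will complete up to 14 web-based training sessions during the four weeks of the training phase".
- **The rule.** At the two-week contact: "If participants have completed fewer than half of the required sessions at this stage (<4) they will be withdrawn from the study". The reason given is compliance.
- **The primary analysis.** "Primary and secondary outcome measures will be analysed using mixed-design ANOVA". The four arms are compared across three measurement occasions: before training, halfway through it and at its end.
- **Sources of drinking data.** During training: "Each time they log on to the site they will be asked how much alcohol they have consumed since their previous session". The Assessment phase section asks participants to keep the online diary for as long as they are in the study. The end-of-training TLFB is taken at the laboratory visit after four weeks (Training phase). The three later TLFB links are timed from the final assessments (Follow up phase).

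The article names no analysis population and no method for missing values.

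**The concern.** The number of sessions completed by week 2 is measured after randomisation, under the allocated task. Removing people on that basis means that the groups compared are no longer the groups randomised. The rule also ends participation in the study, so it stops the collection of the outcome as well as exposure to training. An analysis plan can choose how to treat missing values, but it cannot recover values that the protocol's own rule stops collecting.

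What is at stake is the meaning of both co-primary results. Aims and hypotheses predicts reductions in the three training groups compared with control. A result limited to people who reached the threshold answers a narrower question, and nothing in the article labels it that way. If the people removed differ between arms in how their drinking changes, the group comparison is also distorted, and the data needed to check this will not exist.

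**Working it through.** **1. The threshold.** Up to 14 sessions in four weeks is 14 × 2/4 = 7 by week 2. Half of 7 is 3.5, so fewer than half means 3 or fewer, which agrees with the stated <4. It also agrees with the separate requirement of at least two sessions a week (2 × 2 = 4). The figure is sound. The issue is what follows for those below it.

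**2. Which values a withdrawn participant has.**

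| Time level in the primary ANOVA | Source in the article | Participant withdrawn at week 2 |
|---|---|---|
| Baseline | TLFB and diary before randomisation | Available |
| Two weeks | Log-on question, diary | At most 3 log-ons, so sparse from that source |
| Four weeks | Log-on question, diary, laboratory TLFB | None: no longer in the study |

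The 2, 4 and 6-week links are timed from final assessments that this participant does not have.

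**3. Consequence for the model.** A mixed-design ANOVA with a three-level within-subject factor, as described, uses participants with a value at every level. The term complete-case is not written in the article. It follows from putting the Training phase rule beside the Primary analyses section.

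**4. When the restriction also biases the comparison.** Assume that the least adherent share w of an arm is removed and that adherence has correlation r with a standardised outcome. The mean of those retained shifts by r·φ(z_w)/(1-w), where z_w is the normal quantile at w. The bias in a contrast is the difference between the two arms' shifts.
- With the same w and r in every arm, the difference is 0. In a simulation with no true effect, 67 per arm, 10% removed in each arm and 4,000 runs, the omnibus F test rejected in 0.047 (r = 0.3) and 0.048 (r = 0.5) of runs, against a nominal 0.05.
- With w or r unequal between arms, the difference is generally not 0. For the planned test, r must concern change in drinking, because baseline is itself a time level. The article gives neither w nor r by arm, so no size or direction can be derived.

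**5. Illustration of the restriction.** Assume that a share w of each active arm is withdrawn and gains nothing, that those retained gain δ, and that the comparison is otherwise unbiased.
- All-randomised effect = (1-w)·δ + w·0 = (1-w)·δ.
- Effect in those retained = δ.
- Relative excess = δ/[(1-w)·δ] - 1 = w/(1-w).

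| Assumed w | w/(1-w) |
|---|---|
| 5% | 0.05/0.95 = 5% |
| 10% | 0.10/0.90 = 11% |
| 25% | 0.25/0.75 = 33% |

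The 10% row borrows the attrition expected under Sample size and randomisation. That figure is overall attrition, not the share removed by this rule. The 25% row lies well above anything that the article expects and only shows how the formula behaves.

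**The case against.** **The analysis population and missing-data method may be in a document not shown.** This is fair, and their absence from an article is not the point here. The rule itself is stated, and it removes people from the study. If the full protocol continues outcome collection for them, the article's sentence says otherwise and should be corrected.

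**A minimum-exposure population is defensible.** This is a phase 2 trial of repeated training, and the Background argues that several sessions are needed. That supports reporting such a result under its own label. It does not support making it the only result that the data allow.

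**Adherence may well be similar across arms.** Each task has 200 trials, sessions take about seven minutes, the schedule, reminders and session-linked payment are shared, and participants are not told their allocation even at the end-of-training visit. This largely stands: with equal and equally related loss, the comparison is restricted but not biased. It cannot be verified, though, without outcomes from those removed.

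Stronger readings are tempting, and the article does not support them:
- *A reader might infer that the result describes only people who kept up with training.* The threshold is 4 of about 7 sessions, checked once. Someone who stops after 4 sessions meets no stated criterion at that check.
- *A reader might infer that rising difficulty drives people out of two arms.* Anyone withdrawn has done at most 3 sessions. On the article's per-session calculation their stop-signal delay is at most 250 + 2 × 10 = 270 ms, against a maximum of 380 ms. The tasks still differ in content, but this mechanism is weak.
- *A reader might infer a spurious benefit because low adherers drink more.* A stable difference in drinking level is present at baseline as well as later, so it cancels in the group-by-time test. Only differences in change matter.

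**Conclusion.** The concern holds in a limited form. The rule acts after randomisation and leaves those withdrawn without a four-week value. The primary ANOVA, as described, is therefore restricted to randomised participants with at least 4 sessions by week 2.

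Bias between arms is possible, not demonstrated. It requires that low adherence differ between arms or relate differently to change in drinking. A reader might conclude that the protection of randomisation is lost outright; the article gives no rates by arm that would show this.

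The 11% excess at w = 10% is a difference between two target effects, under the assumption that those withdrawn gain nothing. If training has no effect, the excess is zero and no false positive arises from it.

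The point still needs action before data are collected, because outcomes that were never collected cannot be restored at analysis.

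**What to change.** 1. In the Training phase section, separate access to training from participation in the study. Whatever is decided about access, keep these participants in outcome collection: the end-of-training TLFB and the 2, 4 and 6-week links, timed from the scheduled end of training for anyone without a final laboratory visit.
2. In the Primary analyses section, analyse all randomised participants in their allocated arm. A likelihood-based linear mixed model using every available time point would serve. It is valid under missing at random, which should be stated, since some disengaged participants will not respond.
3. Report the analysis limited to those meeting the session threshold as a labelled per-protocol or sensitivity analysis, with the numbers below the threshold shown by arm.

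The cost is a change of wording, a few more contacts and visits for people already enrolled, and a somewhat diluted effect estimate.

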#### Follow up phase

Participants will be sent a link via email two, four and six weeks after their final assessments. Each link will direct them to a two-week TLFB hosted on Inquisit web. Participants will be offered £5 for each follow-up session completed. Following the final follow-up, all participants (regardless of whether they completed the follow-up assessments) will be sent a full debrief.

A small, random subsample of participants (10) from each active treatment group will be invited back to the University following the final debrief for a semi-structured interview with a researcher about their experiences during the intervention. This interview will include open-ended questions in order to probe their views regarding the accessibility of the training program and any potential barriers to use. We will use qualitative analysis to identify common themes relating to user accessibility and experience.

#### Outcome measures

The pre-defined co-primary outcome measures are (1) the number of units of alcohol consumed, and (2) the number of heavy drinking days, defined as alcohol consumption ≥ 60 g (7.5 UK units) for men and ≥ 40 g (5 UK units) for women [70] on any given day. The number of abstinent days is our secondary outcome measure.

#### Primary analyses

Primary and secondary outcome measures will be analysed using mixed-design ANOVA with a between-subject factor of treatment condition (4: Cue-Specific inhibition training, General inhibition training, Alcohol No-Go training, Control) and a within-subject factor of time (3: baseline, two weeks into training, four weeks into training).

#### Supplementary analyses

If there are group differences in outcome measures at the end of training, we will analyse follow-up data using a separate mixed-design ANOVA with a between-subject factor of treatment condition, and a within-subject factor of time (3: two-week, four-week and six-week follow-up).

The effects of treatment condition on general inhibition, cue-specific inhibition and automatic alcohol-affective associations will be analysed using mixed-design ANOVA with a between-subject factor of treatment condition, and a within-subject factor of time (2: before training vs. after training).

The responses from the subgroup of participants who return to the laboratory for an interview about their experiences of taking part in the trial will be analysed using thematic analyses to identify themes related to treatment efficacy, acceptability and barriers to use (see [71]).

Any further exploratory analyses will be labelled as exploratory in the final publication.

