## Abstract

**Background:**

Problem drinkers have poor inhibitory control (disinhibition). Previous studies have demonstrated that various forms of ‘inhibition training’ can reduce alcohol consumption in the laboratory and at short-term follow-up, but their longer-term efficacy and mechanisms of action are unknown. In this phase 2 randomised controlled trial we will contrast the effects of three forms of inhibition training and a control intervention, delivered via the Internet in multiple sessions over four weeks, on alcohol consumption in heavy drinkers.

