### Aims and hypotheses

The aim of this study is to examine the efficacy of repeated inhibition training as an intervention to reduce alcohol consumption in heavy drinkers recruited from the local community. We will recruit individuals who consume alcohol in excess of UK government guidelines for safe drinking, and who are motivated to cut down [43]. Most heavy drinkers never seek treatment [44, 45], and without treatment they are likely to transition into more harmful patterns of drinking [46]. Heavy drinkers who are not severely alcohol dependent are also less likely to engage with abstinence based treatments [47]. However, a significant proportion of regular drinkers express desires to reduce their alcohol consumption [48]. Therefore a reduction in alcohol consumption is a viable goal for interventions for this population [49, 50].

In order to ensure that they are motivated to reduce their drinking, all participants will complete a brief intervention (‘Down Your Drink’ (DYD) [51]) followed by one week of monitoring of their alcohol consumption before they begin inhibition training. This brief intervention and self-monitoring period are also included in the study for pragmatic purposes. Many heavy drinkers will reduce their alcohol consumption after a brief intervention and/or a period of self-monitoring, and failure to control for these ‘non-specific’ effects can obscure effects of active treatments [52, 53].

Participants will be randomly allocated to one of four groups: 1. General inhibition training; 2. Cue-Specific inhibition training; 3. Alcohol No-Go training; or 4. Control. All participants will complete an internet intervention 14 times over a four-week period (every other day, on average). Their alcohol consumption will be monitored throughout the training period. We predict reductions in alcohol consumption during the training period in the first three groups compared to the control group. This will be the first study to directly compare these three types of inhibition training, so we have no *a priori* hypotheses about which will produce the largest reduction in alcohol consumption.

We will monitor participants’ alcohol consumption at two, four and six-weeks after the end of the intervention (follow-up). We predict that any group differences in alcohol consumption that are seen at the end of the training period will be maintained throughout the follow-up period.

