#### Sample size and randomisation

We used G*Power 3.1.5 [55] to calculate the required sample size for power of 0.80 to detect any main effect or interaction (numerator df = 3) at an alpha level of 0.05 (see Table 1). We based this calculation on a recent meta-analysis concerning e-help interventions for problem drinkers [41] which demonstrated a medium effect size (f = 0.25). As seen in Table 1 we require a total sample size of 179 to detect an effect.

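### Follow-up drinking is tested only if arms differ at the end of training, in a model without baseline or end-of-training data, so longer-term efficacy is tested conditionally and inefficiently and maintenance is not formally tested

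*Protocol article*

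**What the plan says.** Protocol article, Supplementary analyses: "If there are group differences in outcome measures at the end of training, we will analyse follow-up data using a separate mixed-design ANOVA". The factors are treatment condition and "a within-subject factor of time (3: two-week, four-week and six-week follow-up").

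Primary analyses: the main ANOVA has "a within-subject factor of time (3: baseline, two weeks into training, four weeks into training"). It contains no follow-up time.

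Follow up phase: "Participants will be sent a link via email two, four and six weeks after their final assessments". The data are therefore requested from participants whatever the end-of-training result.

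Aims and hypotheses: the prediction is that "any group differences in alcohol consumption that are seen at the end of the training period will be maintained throughout the follow-up period".

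Abstract, Background: of earlier forms of inhibition training it says that "their longer-term efficacy and mechanisms of action are unknown".

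The precondition does not say which outcome (there are two co-primary outcomes and one secondary), which test or which threshold counts as a group difference.

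**The concern.** Two features of the stated plan do not fit its aims.

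**The model.** Maintenance is a statement about two time points: the arm contrast at follow-up set against the same contrast at the end of training. No planned model holds both. The treatment-by-time term in the follow-up ANOVA asks only whether the arms change relative to one another among weeks 2, 4 and 6 after training. An effect that had gone by the first follow-up leaves no trace in it. Baseline drinking is also left out, which gives up precision.

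**The precondition.** Whether follow-up is tested at all depends on a significance result at another time. An effect that is modest but lasting, or that appears after training, may have no planned follow-up test. Longer-term efficacy is the gap that the abstract names, and the data to address it will have been collected.

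**Working it through.** **Inputs from the protocol article (Sample size and randomisation, Table 1).** Four groups, f = 0.25, alpha 0.05, numerator df 3, required N 179, planned N 268 (67 per group), up to 33% excluded as early reducers if necessary, about 10% attrition.

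**Assumptions not in the document.** Normal data, SD 1 at each time, the same correlation ρ between any two times, no missing data, and three active arms equally better than control by d, so that f = d√3/4. Hence f = 0.25 means d = 0.577, and d = 0.4 means f = 0.173 (f² = 0.03).

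**1. The plan's own figure.** Noncentral F with λ = f²N, df 3 and N − 4. At N = 179, λ = 0.0625 × 179 = 11.1875, critical F 2.6562 and power 0.8015. Table 1 reproduces exactly.

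**2. How often a true f = 0.25 effect misses the precondition, read as a one-way test.**

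| N | Derivation | λ | Power | Missed |
|---|---|---|---|---|
| 268 | as planned | 16.75 | 0.941 | 5.9% |
| 241 | 268 × 0.90 | 15.06 | 0.913 | 8.7% |
| 179 | 268 × 0.67 | 11.19 | 0.802 | 19.8% |
| 161 | 268 × 0.90 × 0.67 | 10.06 | 0.752 | 24.8% |

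**3. Power of the follow-up main effect, with and without baseline.** The mean of three follow-ups has within-arm variance v = (1 + 2ρ)/3. Adjusted for baseline it is v − ρ². Then λ = N f²/variance. With 45 per arm (N = 180) and d = 0.4, N f² = 5.4:

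| ρ | v | λ | Power | v − ρ² | λ | Power |
|---|---|---|---|---|---|---|
| 0.5 | 0.667 | 8.10 | 0.65 | 0.417 | 12.96 | 0.86 |
| 0.7 | 0.800 | 6.75 | 0.56 | 0.310 | 17.42 | 0.95 |
| 0.8 | 0.867 | 6.23 | 0.53 | 0.227 | 23.82 | 0.99 |

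Simulation of the same cases gave 0.662, 0.554 and 0.527 without baseline, and 0.862, 0.946 and 0.984 with it. At the planned f = 0.25 and 45 per arm, N f² = 11.25 and the unadjusted test has power 0.94, 0.89 and 0.86 at the three correlations.

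**4. Whether the planned terms see a loss of effect.** Simulation, 1,500 runs per case, 45 or 67 per arm, ρ 0.5 or 0.7, f = 0.25 during training and nothing at follow-up. The planned follow-up treatment-by-time term was significant in about 5% of runs, which is its false-positive rate. A direct interaction of arm with end of training versus mean follow-up was significant in 94 to 100%. As a check, the variance of that change is (1 − ρ) × 4/3. At 45 per arm and ρ = 0.5 this gives λ = 11.25/0.667 = 16.9 and power 0.94. If half the effect is lost, λ falls to a quarter, and the direct test has power 0.37 (45 per arm, ρ = 0.5) to 0.78 (67 per arm, ρ = 0.7).

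**5. The whole planned sequence.** Same simulation, with the precondition read as a significant treatment-by-time interaction in the primary ANOVA:

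| True effect | Passes precondition and significant at follow-up | Same data, no precondition |
|---|---|---|
| f = 0.25, maintained | 79 to 98% | 99 to 100%, baseline-adjusted |
| Half that size, maintained | 8 to 28% | 56 to 87%, baseline-adjusted |
| f = 0.25, only after training | 4 to 5% | 89 to 99%, unadjusted |

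**The case against.** The strongest defence is that the plan does what its hypothesis asks. The maintenance prediction is itself conditional: with no difference at the end of training there is nothing to maintain. The efficacy prediction concerns the training period, follow-up is labelled supplementary, and the remark on longer-term efficacy describes earlier studies. This stands as far as it goes. The precondition is consistent with the Aims. It sits badly only with the wider question of longer-term efficacy, and a late effect is not a stated hypothesis.

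A reader might infer that longer-term efficacy cannot be tested at all. The document does not support that. Once the precondition is met, the treatment main effect is a valid randomised comparison over the six weeks. Leaving out baseline costs power but adds no bias. If the effect had vanished, that main effect would be null in expectation, and nothing in the text says that the investigators would look only at the interaction.

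A reader might also infer that a fifth to a quarter of trials with a real effect throw their follow-up data away. That rate holds only after the full exclusion of early reducers, which is to be made only if needed. Labelled exploratory analyses also remain open. Nor does the precondition inflate error under a global null: a planned follow-up finding then needs both tests to be significant, which cannot happen more often than the follow-up test alone.

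What the defence does not answer: the change from end of training to follow-up has no planned test, baseline is unused, and the precondition is undefined.

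**Conclusion.** The point holds in a limited form. Longer-term efficacy is tested only conditionally and with avoidable loss of power, and maintenance relative to the end of training is not formally tested. The main effect can show that arms still differ, but not whether the difference has shrunk since training ended.

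The cost depends on the case. For the planned effect, fully maintained, it is small to moderate: a one-way precondition is missed 6 to 9% of the time at N = 268 to 241, and 20 to 25% at N = 179 to 161. For smaller or later effects it is large, as the sequence simulation shows. The miss rates rest on the protocol's own F test and on reading the precondition as that test, which the protocol does not state. The follow-up power figures and simulations rest on assumed correlations, equal active arms and complete data.

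This does not invalidate the trial or its primary analysis. It should be changed because the change is cheap and lets the plan test its own prediction.

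**What to change.** Replace the conditional sentence in Supplementary analyses. Analyse the 2, 4 and 6-week data whatever the week-4 result, in one baseline-adjusted repeated-measures model that also includes the end-of-training time point. Report, with 95% CIs, each active-versus-control contrast at six weeks and the change in that contrast from the end of training to six weeks. The second is the test of maintenance.

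If error control is wanted, make the confirmatory claim, not the analysis, conditional on the end-of-training result, and name the outcome, test and threshold that decide it.

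The cost is a change of wording and slightly more analysis work, with data already due to be collected. The one downside is that follow-up results reported after a null week-4 result must be labelled as supplementary.

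### The three mechanism outcomes are tested by a before/after ANOVA, equivalent to a change-score test; adjusting for the pre-training value already collected would be more precise at almost no cost.

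*Protocol article*

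**What the plan says.** The protocol article, Supplementary analyses, states: "The effects of treatment condition on general inhibition, cue-specific inhibition and automatic alcohol-affective associations will be analysed using mixed-design ANOVA". The between-subject factor is treatment condition (four arms), crossed with "a within-subject factor of time (2: before training vs. after training"). No covariate is named, and the section does not say which term of the ANOVA carries the treatment test.

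The measurements are paired. At the return visit (Assessment phase), participants who stay in the study "will complete baseline measures of the general SST, cue-specific SST and the AV-IAT in the laboratory". After four weeks of training (Training phase), "They will also complete the SSTs (cue-specific and standard) and AVIAT in the laboratory once more".

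Allocation comes after the baseline tasks in the order of the text. The Training phase, which follows the Assessment phase, opens with "Participants will be randomised to one of four experimental groups", and Sample size and randomisation places random assignment after the initial one-week period.

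**The concern.** In a 4 x 2 layout, two terms involve condition. The condition main effect compares the mean of the before and after values, so an effect present only after training is halved. The condition-by-time interaction is the natural test, and with two time points it is a test on after-minus-before differences. Subtraction fixes the weight of the baseline at one. Regression on the baseline uses the weight that the data support, and so leaves no more residual variance.

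What is at stake is the set of arm-specific predictions under Aims and hypotheses: No-Go training alters alcohol associations, General training improves inhibition broadly, and Cue-Specific training improves it for alcohol cues only. A selective pattern of this kind is read partly from effects that are not found. Avoidable noise makes it more likely that a real effect is missed and that the arms look more distinct in mechanism than they are.

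**Working it through.** **The plan's own figure.** Table 1 was reproduced from the noncentral F distribution with lambda = N x f². The inputs are from Sample size and randomisation: "power of 0.80 to detect any main effect or interaction (numerator df = 3) at an alpha level of 0.05", four groups, f = 0.25. With N = 179, lambda = 179 x 0.0625 = 11.1875, error df = 175, critical F = 2.6562 and power = 0.8015. N = 178 gives 0.7990, so 179 is the smallest adequate total and Table 1 is right as computed.

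**Equivalence.** On a simulated data set of 180 subjects in four groups, the condition-by-time F of the mixed ANOVA and the one-way F on change scores were both 0.22698.

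**Error variance.** Let the SDs before and after be s1 and s2, with within-arm correlation rho.
- Change score: s1² + s2² − 2·rho·s1·s2
- Baseline-adjusted: s2²(1 − rho²)
- Difference: (s1 − rho·s2)², which is never negative

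The direction therefore does not depend on equal SDs; the percentages do. With s1 = s2 = 1 the two variances are 2(1 − rho) and 1 − rho², their ratio is (1 + rho)/2 and the reduction is (1 − rho)/2.

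| Assumed rho | Change score | Adjusted | Reduction |
|---|---|---|---|
| 0.3 | 1.40 | 0.91 | 35% |
| 0.5 | 1.00 | 0.75 | 25% |
| 0.7 | 0.60 | 0.51 | 15% |
| 0.8 | 0.40 | 0.36 | 10% |
| 0.9 | 0.20 | 0.19 | 5% |

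Simulation (180 subjects, 1000 runs per value) gave 35.1%, 24.9% and 15.1% for rho of 0.3, 0.5 and 0.7.

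**Illustrative power.** Take f = 0.25 on the post-training SD. Then lambda = N x 0.0625 divided by the error variance above. Error df are N − 4 for the change score and N − 5 for the adjusted analysis. Two totals are used: 179, the required number, and 268 x 0.9 = 241.2, about 241, the planned total less the expected 10% attrition.

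| Assumed rho | N = 179: lambda | N = 179: power | N = 241: lambda | N = 241: power |
|---|---|---|---|---|
| 0.3 | 7.99 vs 12.29 | 0.64 vs 0.84 | 10.76 vs 16.55 | 0.79 vs 0.94 |
| 0.5 | 11.19 vs 14.92 | 0.80 vs 0.91 | 15.06 vs 20.08 | 0.91 vs 0.97 |
| 0.7 | 18.65 vs 21.94 | 0.96 vs 0.98 | 25.10 vs 29.53 | 0.99 vs 1.00 |

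(Each pair is change score vs adjusted.)

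The article does not say on which scale f is defined. If 0.25 is read on the change-score scale, power at N = 179 rises from 0.80 to 0.95, 0.91 and 0.87 at rho of 0.3, 0.5 and 0.7, and the total needed for 80% power falls from 179 to 118, 135 and 153.

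**The case against.** The strongest reply is that nothing here is wrong. A before/after mixed ANOVA is an unbiased, valid test in a randomised trial, it describes improvement directly, which is how the hypotheses are worded, and the outcomes are neither primary nor secondary. This stands. A reader might infer that the mechanism results would be biased or that the efficacy conclusion is affected; the documents support neither.

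A reader might also take a gain of 15 to 35% as established. It is not. That range is only what rho of 0.7 to 0.3 produces under equal SDs, and the article reports no correlation and no SD for any of the three measures. Nor does it say anything about how repeatable these tasks are, so there is no ground for favouring the low-rho, large-gain end.

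Finally, a reader might conclude that the mechanism analyses are underpowered. The article does not support this either. Its f comes from a meta-analysis of e-help interventions for problem drinkers, said to have "demonstrated a medium effect size (f = 0.25"); it was not derived for SSRT or the D score. The statement "we require a total sample size of 179 to detect an effect" gives the number before inflation to 268. That inflation allows for excluding early reducers from the primary analyses because of a floor effect in drinking, and no such exclusion is stated for the mechanism outcomes. About 241 may therefore be the more relevant total, and there the gap is sizeable only at the lowest of the three correlations.

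The adjusted analysis also costs one error degree of freedom. At 175 this is negligible.

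**Conclusion.** The point holds as an efficiency improvement. The planned interaction test is a change-score test, and the baseline needed for a more precise analysis is measured on the same three tasks and, by the order of the text, before allocation. With a common slope across arms, the adjusted error variance is no larger whatever the SDs, and with equal SDs it is smaller for any rho below 1.

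The size is open, because it rests on an assumed rho: from a 35% reduction at 0.3 down to 5% at 0.9. The power figures are illustrative and shrink towards no difference at high rho or at the larger N. What is lost is precision on supplementary outcomes, with no bias and no bearing on the co-primary outcomes.

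**What to change.** In Supplementary analyses, state that for each of standard SSRT, cue-specific SSRT and the AVIAT D score, the after-training value will be modelled with treatment condition as factor and the before-training value of the same measure as covariate. Report adjusted differences from Control with 95% CIs, which also address the arm-specific predictions more directly than an omnibus interaction F. Keep the before/after ANOVA as a descriptive summary of change.

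The cost is one sentence of wording and one error degree of freedom. No new data, visits or participants are needed.
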